## Methods

### Design

Our study has a practice-based nature. Carrying out research in a setting such as a JJI is challenging, as it is in most practice-based studies [25]. It is virtually impossible to organize a randomized controlled trial in a JJI. First, judges are not likely to agree with randomizing adjudicated adolescents to different detention conditions. Second, JJIs struggle with relative instability of staff due to high turnover and high rates of absenteeism [26]. Another barrier for conducting research in JJIs is the unfamiliarity among most of the institution’s staff with the principles and benefits of research studies [23]. To prepare JJI personnel for implementing and evaluating FC, we trained them to internalize FC rationale and FC practice and we organized a seven-month pilot stage. In the remainder of the pilot stage, we found FC short-term stay groups to differ in number and nature of family-oriented actions, although all group workers had received the same training. Also, we noticed that not every parent visited their child or attended every kind of family activity organized by the JJI. Additionally, the preliminary analyses of the pilot data showed the surprising finding that most parents and youths report few family problems, while at the same time they report motivation for family therapy. In setting up the actual study, we used feedback from staff and the results of monitoring the groups during the pilot stage to improve the FC program.

Evaluating the pilot stage gave rise to our final study design, in which the pilot is considered as the first stage, see Figure 1.

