### Recruitment and Sample Size

Adolescents and parents are informed of the JJI’s research activities by a flyer in the information leaflets from the JJI. The flyer informs that the data will be used anonymously in research studies and that parents can address their questions concerning these activities to their child’s mentor (one of the group workers) or to the psychologist.

The JJIs in the Netherlands jointly apply ROM and standard screening and diagnostic procedures for detained adolescents and their parents. As our assessments will be embedded in these procedures, the quantitative part of our study will use data collected in the two participating JJIs by these means. Recruitment of adolescents and their parents in the quantitative part of our study will last 21 months, including the pilot stage of 7 months. Based on records from 2011, the year prior to the pilot stage, we estimate that in 21 months, 300 adolescents will be placed in the groups concerned. Taking into account the exclusion criteria, we expect to recruit 160 adolescents and parents for the present study. Based on previous research, this number suffices for establishing statistically significant differences on quantitative measures between the two conditions [9].

As for qualitative studies, 10 interviews are generally sufficient to achieve saturation (ie, the point where additional interviews do not yield new essential information regarding the research question) [32]. Once an eligible adolescent is placed in a short-term stay group (either FC or UC), he and his parents will be invited to participate in the qualitative part of the study. If they are willing to participate, an appointment will be made for the interview. We will interview 10 boys (5 aged < 16 years and 5 aged > 16 years) in each JJI (N=20). We will also interview 20 parents (10 in in each JJI, 10 fathers and 10 mothers, 10 with a detained child aged < 16 years, and 10 with a detained child aged > 16 years). Finally, we will interview 20 FC group workers and 20 UC group workers.

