### Analyses

#### Quantitative Analyses

All statistical analyses will be performed using SPSS 23. In a future paper, we will provide a flowchart of participants in our study, including reasons for exclusion. Descriptive statistics will be presented as means and standard deviations for all continuous variables and subscales. Additionally, frequency distributions or qualitative descriptions of all categorical variables will be presented for each group. The groups will be defined as FC or UC. We will test if these groups differ on demographic factors. If these differences exist, we will use these factors as covariates in our analyses. If necessary, we will also include the JJI in which an adolescent is placed as a covariate. We will perform within-group pre-post comparisons, between-group comparisons (FC vs UC), and repeated measures analyses. The selection of a specific test will depend on which hypothesis is tested and on the characteristics of the corresponding data (eg, categorical, ordinal, or interval level and normally or non-normally distributed). Table 3 shows the planned analyses to test our hypotheses for comparing FC with UC in case of normally distributed data. For combining the within-group pre-post comparisons and the between-group comparisons in our analyses, we will use the repeated measures ANOVA. Because the normality of the distribution of the data cannot be determined beforehand, the final analyses will be selected after the data is gathered. In analyzing the hypotheses, two-tailed analyses will be performed and we will correct for multiple testing.

**Table 3 table3:** Planned analysis for between-group hypotheses.

Hypothesis	Data source	Analysis
FC increases parents’ involvement with their detained child	Registration logs visits	Unpaired *t* test
FC increases the motivation of the adolescents and parents for accepting treatment and guidance by JJI staff and for taking part in family meetings	ATMQ youth total score Motivation items youth	Unpaired *t* test Pearson’s Chi-square test
	Motivation items parents	Pearson’s Chi-square test
FC adolescents show less problem behavior	Incidents in JJI Cannabis database	Unpaired *t* test Unpaired *t* test
FC improves family interactions	FES	Unpaired *t* test
FC parents experience less parenting stress	PSQ	Pearson’s Chi-square test
FC youth more often return to their families’ home upon discharge	Registrations logs living situation after discharge	Pearson’s Chi-square test

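### Final tests are to be chosen after data collection on grounds of normality, although the data type of visits, incidents and cannabis screens already settles the question, and no deciding analysis per hypothesis is named

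*Protocol article*

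**What the plan says.** All points are in the protocol article.

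- **Timing and reason (Quantitative Analyses).** "Because the normality of the distribution of the data cannot be determined beforehand", "the final analyses will be selected after the data is gathered".
- **Criteria (same section).** "The selection of a specific test will depend on which hypothesis is tested and on the characteristics of the corresponding data", meaning measurement level and whether the distribution is normal. No normality criterion and no alternative test is named.
- **Defaults.** "Table 3 shows the planned analyses to test our hypotheses for comparing FC with UC in case of normally distributed data". The table gives unpaired t tests for visits, incidents, cannabis, the FES, the ATMQ total score and Satisfaction part B. It gives chi-square tests for the motivation items, PSQ, living situation and Satisfaction part A. The staff questionnaires get generalized estimating equations (part A) and a repeated measures general linear model (part B).
- **Parallel analyses.** The text also plans within-group pre-post comparisons and a repeated measures ANOVA that combines these with the between-group comparison. Demographic covariates enter if the groups differ on them, and JJI enters if needed.
- **Error control.** "two-tailed analyses will be performed and we will correct for multiple testing". The method and the family of tests are not named.
- **Outcome types.** Involvement is a number of visits plus logged telephone contacts. Problem behavior comes from recorded incidents. Cannabis use comes from urine screens taken at scheduled and random times.
- **Exposure.** Stays under 14 days are excluded (Participants). Pre-trial detention customarily lasts at most 90 days (Setting).
- **Status.** The Discussion says that data collection ended in 2015 and that first outcomes were being analysed.

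**The concern.** The article does not merely leave the choice of test for later. It states that the choice follows the data. The reason given is an unknown distribution, but for three Table 3 data sources the distribution type is known from how they are recorded. A count of visits or incidents, or a set of positive and negative screens, is discrete, bounded at zero and dependent on how long the boy was there. A longer stay gives more visits, incidents and screens whatever the program does. A t test on raw counts ignores this, and checking normality afterwards would not reveal it.

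The article also offers two routes to the same group comparison: the Table 3 between-group test and the repeated measures ANOVA. It does not say which one answers the hypothesis. Two analyses of one hypothesis can disagree. If the choice between them is made with results in view, the nominal level no longer describes that hypothesis. A multiplicity correction across hypotheses counts each hypothesis once, so it does not pay for alternatives tried within one.

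**Working it through.** **Inputs.** The expected sample is 160 (Recruitment and Sample Size). Setting describes three FC and two UC groups. If groups fill equally, which is an assumption, the split is 160 × 3/5 = 96 and 160 × 2/5 = 64. The article states no significance level, so two-sided 5% is assumed. It gives no baseline-exit correlation, so 0.5 is assumed and 0.3 to 0.7 is shown. It states no error rate under flexible choice, so there is no figure of its own to reproduce.

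**Step 1: is normality really open for the counts?** Null data were simulated with 10,000 replicates per scenario, at 80:80 and 96:64. The counts were Poisson (mean 2) and two overdispersed negative binomials (mean 2, dispersion 0.5; mean 0.5, dispersion 0.3). Shapiro-Wilk rejected normality in 100% of replicates for every count distribution. For such outcomes the result of the check is known before any data arrive.

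**Step 2: what does the choice between t and rank test cost?** The same runs, with normal and log-normal outcomes added, gave these type I error rates:

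| Strategy | Type I error |
|---|---|
| t test fixed in advance | 4.4 to 5.3% |
| Mann-Whitney fixed in advance | 4.9 to 5.2% |
| Shapiro-Wilk decides between them | 4.9 to 5.3% |
| Smaller p-value of the two | 6.0 to 7.9% |

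The upper end of the last row comes from the strongly overdispersed counts. A separate run at 96:64 with 6,000 replicates gave 5.9% (normal) and 7.4% (log-normal) for the smaller p-value.

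**Step 3: what does leaving the deciding analysis open cost?** With two time points, the group-by-time test of the repeated measures ANOVA is equivalent to a t test on change scores (F = t²). For unit variances and baseline-exit correlation ρ:

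- Var(change) = 2(1 − ρ)
- Cov(exit, change) = 1 − ρ
- Corr(exit, change) = √((1 − ρ)/2), which is √0.25 = 0.5 at ρ = 0.5

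The chance that at least one of two standard normal statistics with this correlation exceeds 1.96 in absolute value is 1 − P(|Z₁| < 1.96 and |Z₂| < 1.96):

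| ρ | Corr(exit, change) | Either significant |
|---|---|---|
| 0.3 | 0.592 | 8.78% |
| 0.5 | 0.500 | 9.07% |
| 0.7 | 0.387 | 9.35% |

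Simulation at ρ = 0.5 and 96:64 with 6,000 replicates gave 8.8% (normal) and 8.2% (log-normal). For normal data this agrees with the formula within simulation error: √(0.09 × 0.91/6000) ≈ 0.4 percentage points.

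**Step 4: exposure.** The longest customary stay is 90/14 ≈ 6.4 times the shortest eligible one. Raw counts mix a rate with a time at risk that can differ more than sixfold between boys.

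**Limits.** The simulations treat boys as independent, with no clustering by living group, and use assumed distributions because the article gives no outcome means or standard deviations.

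**The case against.** The strongest reply is that the choice is tied to data characteristics and not to results, that tests are two-tailed and multiplicity is corrected, and that Table 3 gives every hypothesis a default. This largely stands. A reader might infer that type I error is uncontrolled. The documents do not support that: step 2 shows that a mechanical normality rule stays near 5%, and the article nowhere says that tests will be picked by p-value. What remains is that nothing in the text rules this out.

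Some further inferences should also be resisted:

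- **That the pilot had already settled normality.** Design mentions only that "the preliminary analyses of the pilot data showed the surprising finding" about reported family problems and motivation for family therapy. It does not say that the distributions of visits, incidents or screens were examined. Recruitment "will last 21 months, including the pilot stage of 7 months", so pilot cases belong to the sample and are no independent basis for choosing tests.
- **That most outcomes are affected.** Three-point items already have chi-square tests. The argument from data type concerns visits, incidents and cannabis screens.
- **That a rank test would remove the covariate adjustment.** The default unpaired t test has no covariates to lose, the article names no rank test, and the covariates are themselves conditional.

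It can also be said that a condensed article leaves normality criteria and fallback tests to a fuller plan. That is fair for the missing detail. It does not answer the sentence itself, which positively sets the choice after data collection, or the t tests that Table 3 fixes for counts.

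**Conclusion.** The point holds in limited form. The stated reason for deferring the choice does not apply to visits, incidents and cannabis screens. Their default t tests also ignore exposure over stays of 14 to about 90 days. For outcomes measured twice, the deciding analysis is not named.

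Applied mechanically, the rule does little harm to type I error. Applied with results in view, one hypothesis could carry about 6 to 7% (t or rank test; close to 8% for strongly overdispersed counts) or about 9% (exit t test or repeated measures interaction) in place of 5%. These sizes rest on a 96:64 split, a correlation of 0.5, a 5% level and independent observations. They describe what the wording permits. They are not evidence of what was done. The change should be made: it is inexpensive, and for the count outcomes it also gives a better analysis.

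**What to change.** Delete the sentence that defers the choice, and name one deciding analysis per outcome by data type:

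- **Visits and incidents:** negative binomial model with log days of stay as offset.
- **Cannabis:** positive screens out of screens taken, in a model for proportions.
- **Scale scores measured at both times:** linear model for the exit score adjusted for baseline, with robust or bootstrap standard errors. It replaces the choice between exit t test and repeated measures ANOVA.
- **Return home:** logistic model.

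Each of these should carry JJI and the planned covariates. Keep the Table 3 analyses for the three-point items and the staff questionnaires. Any other analysis of the same outcome becomes supportive and is labelled so.

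The cost is analysis wording. The models are available in SPSS, and no new assessment is needed beyond extracting days of stay and number of screens from the institutions' records. Because data collection had ended and first outcomes were being analysed when the article was written, rewording cannot restore choice made before the data. The report should therefore state which models were chosen after that point and show the Table 3 result alongside them.

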#### Parenting Stress

We will use the Parenting Stress Questionnaire (PSQ, in Dutch: Opvoedingsbelasting Vragenlijst, OBVL) [37] for assessing the level of parenting stress experienced by parents. The PSQ targets individual characteristics of parents in relation to parenting and to the quality of the parent-child interaction. The questionnaire consists of 34 items to be scored on a four-point scale. Its five subscales are Parent-child relationship problems, Parenting problems, Depressive mood, Parental role restriction, and Physical health problems. The PSQ is shown to be reliable and valid. The Cronbach alphas for the five subscales are .84, .83, .83, .79, and .78 respectively. The total scale was also found reliable (alpha=.90) [38].

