#### Satisfaction

We devised a questionnaire based on the Satisfaction Scale [39] and the Client-test (C-test, in Dutch: C-toets [40]), which we will use to determine how satisfied the adolescents and parents are with the JJI. These two questionnaires are shown to be reliable and valid [39,41]. Regarding the Satisfaction Scale for parents, all subscales for the inpatient/residential treatment center population demonstrate good internal consistency, with Cronbach alphas ranging from .76 to .94. For children, all subscales for the inpatient/residential treatment center population show good internal consistency, with Cronbach alphas ranging from .78 to .91, except subscale Access and convenience (alpha=.63) [39]. Cronbach alphas for the four subscales of the parent versions of the Client-test demonstrate good internal consistency, ranging from .77 to .90. The total questionnaire is found to be reliable (alpha=.94). The children version only has a total scale, which is found to be reliable (alpha=.91) [41]. Our satisfaction questionnaire has two parts, part A and part B. Part A contains 14 items to be rated on a three-point scale. It includes items such as “The staff members are friendly”, “I feel that the staff members are interested in me”, “The staff members treat me with respect”, and “The staff members help me dealing with problems”. Part B contains one question, “All things considered, which grade would you give to the service provided by the JJI?”, to be rated on a scale of 1-10.

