FC enhances adolescents’ and parents’ satisfaction with the JJI	Satisfaction questionnaire-A Satisfaction questionnaire-B	Pearson’s Chi-square test Unpaired *t* test
In FC groups, JJI staff members are more satisfied, feel more confident in their contact with parents, and more often incorporate the family perspective in thinking	Questionnaire staff-A	Generalized estimating equations
	Questionnaire staff-B	General linear model repeated measures

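### Table 3 tests parenting stress, a 34-item scale with a reliable total score, by Pearson chi-square on undefined categories; test the score instead

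*Protocol article*

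**What the plan says.** Protocol article, Quantitative Analyses, Table 3: the row for hypothesis 5, "FC parents experience less parenting stress", lists the PSQ as its only data source and Pearson's chi-square as its test. The table is introduced thus: "Table 3 shows the planned analyses to test our hypotheses for comparing FC with UC in case of normally distributed data".

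Parenting Stress section: "The questionnaire consists of 34 items to be scored on a four-point scale". It names five subscales and adds: "The total scale was also found reliable (alpha=.90"). It gives no cut-off, band or other category for the PSQ, and neither does any other section.

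Elsewhere in Quantitative Analyses, continuous variables and subscales are to be summarised by means and standard deviations. A repeated measures ANOVA is to combine the pre-post and between-group comparisons. The final choice of test waits for the data because normality cannot be known beforehand. On adjustment: "If these differences exist, we will use these factors as covariates in our analyses", and "If necessary, we will also include the JJI in which an adolescent is placed as a covariate".

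For the secondary remark, the satisfaction row of Table 3 reads "Satisfaction questionnaire-A Satisfaction questionnaire-B", with chi-square for part A and a t test for part B. The Satisfaction section says of part A: "Part A contains 14 items to be rated on a three-point scale".

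**The concern.** A Pearson chi-square test needs categories. To apply it to the PSQ, someone must cut the score into bands that the article does not define, and the test then ignores both the order of the bands and all differences within them. The hypothesis is about degree (less stress), which a mean difference answers directly.

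The PSQ is the sole source for hypothesis 5, so no better-analysed measure stands behind it. The article also appears to treat the same instrument in two ways: as continuous in the descriptive summaries and, if it is included there, in the repeated measures ANOVA, but as categorical in the between-group test. It does not say which result decides the hypothesis. A cut chosen after the data are in would also leave room for a data-dependent choice.

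**Working it through.** **Step 1. Compare how Table 3 treats similar instruments.**

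| Instrument | Format described | Scale score named? | Table 3 test |
|---|---|---|---|
| PSQ | 34 four-point items, five subscales | yes, total (alpha .90) | chi-square |
| Family Environment Scale (FES) | subscales of 11 yes/no items, two dimensions | yes | t test |
| Adolescent Treatment Motivation Questionnaire (ATMQ) | 11 three-point items | yes, total | t test |
| Satisfaction-A | 14 three-point items | no | chi-square |
| Added motivation items | separate items | no | chi-square |

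The table follows a recognisable rule: an instrument with a named score gets a t test, and separate items get chi-square. The PSQ is the exception. Its total can take up to 34 × 3 + 1 = 103 values, so a chi-square on uncut scores from about 160 families is not workable and a cut is implied.

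**Step 2. Size the loss.** The article's only design figure is the expected 160 (Recruitment and Sample Size). It cannot be reproduced, because no alpha, power, effect size or SD is given, only a citation. It serves here purely as an input.

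Inputs from the article: 160; three family-centered (FC) groups and two usual-care (UC) groups (Setting).

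Assumptions not in the article: one PSQ score per family; split in proportion to groups, 160 × 3/5 = 96 FC and 64 UC; normal score; two-sided alpha 0.05; true difference d = 0.3 to 0.5 SD; no clustering; no multiplicity correction; one cut, placed so that 50%, 20% or 10% of UC parents lie above it.

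*t test:* power = Φ(d / √(1/64 + 1/96) − 1.96), where the root is 0.1614.
- d = 0.3: Φ(1.859 − 1.96) = 46%
- d = 0.4: Φ(2.479 − 1.96) = 70%
- d = 0.5: Φ(3.098 − 1.96) = 87%

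*Chi-square after one cut:* let p₁ be the UC share above the cut c, p₂ = 1 − Φ(c + d) the FC share, and p̄ their weighted mean. Then power = Φ{ [ |p₁ − p₂| − 1.96 √(p̄(1 − p̄)(1/64 + 1/96)) ] / √(p₁(1 − p₁)/64 + p₂(1 − p₂)/96) }.

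Worked case, median cut and d = 0.5: p₁ = 0.5000, p₂ = 0.3085, p̄ = (64 × 0.5000 + 96 × 0.3085)/160 = 0.3851. The difference is 0.1915, the null term 1.96 × 0.0785 = 0.1539, and the denominator 0.0783. So (0.1915 − 0.1539)/0.0783 = 0.48 and power is 68%.

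| d | t test | median cut | 80/20 cut | 90/10 cut |
|---|---|---|---|---|
| 0.3 | 46% | 31% | 25% | 19% |
| 0.4 | 70% | 50% | 38% | 28% |
| 0.5 | 87% | 68% | 52% | 37% |

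**Step 3. Checks.**
- Retained information for small effects is φ(c)²/[q(1 − q)], with q the share above the cut: 0.3989²/0.25 = 64%, 0.2800²/0.16 = 49%, 0.1755²/0.09 = 34%. Multiplied by 160, that is 102, 78 and 55 families.
- With an 80:80 split and d = 0.5: 88% for the t test against 70%, 51% and 35%.
- More bands do not rescue the test. In 2,000 simulated trials at 96:64 and d = 0.5, chi-square on ten score bands reached 50% power against 86% for the t test.

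**The case against.** Table 3 is not the whole plan. The repeated measures ANOVA could analyse the PSQ as a continuous outcome with covariates, and the final tests are left open. A reader might infer from the chi-square cell that hypothesis 5 will be tested with low power and without adjustment. The article does not support that as a certainty. What remains is that the openness is tied to normality: Table 3 already states the normal case, and a non-normal score would point to a rank test rather than chi-square. The ANOVA and the PSQ cell still need reconciling.

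A reader might also charge that chi-square cannot carry the promised covariates. That is true but not specific to this row, because the unpaired t tests in the same table take none either. It is no separate fault here.

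Nor does the table's normality caption convict the cell by itself. The same table gives chi-square to living situation after discharge, which is plainly categorical, so the caption cannot govern every row.

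It is tempting to bring the same charge against Satisfaction-A. The article names no total for it, and the alphas it reports belong to the source instruments, so item-by-item testing is a plausible intention. A count of 14 items × 2 informants = 28 tests is only one reading, and a correction for multiple testing is promised. The point that stands is smaller: Pearson's chi-square ignores the order of the answers.

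Finally, clinical PSQ cut-offs may be intended and stated in a document not shown. The Design section also reports that most pilot families described few family problems, so a normal PSQ score is not assured. Both are reasons to treat the power figures as illustration.

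**Conclusion.** The point holds for the PSQ. Table 3 gives it a test for categories although the article describes a scale with a reliable total, defines no categories, uses t tests for comparable scales, and plans an ANOVA that would treat such a score as continuous. If the cell is followed, information is lost on the only measure of hypothesis 5.

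Under the stated assumptions the loss is about 15 percentage points of power at its smallest (46% to 31%: d = 0.3, median cut) and 50 at its largest (87% to 37%: d = 0.5, 90/10 cut). The direction of the loss does not depend on the chosen d or cut within that range; its size does. Clear non-normality would change the figures.

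For Satisfaction-A and the three-point motivation items there is only a minor remark about unused order. This is a correction that should be made, not one that undermines the study.

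**What to change.** Replace the PSQ cell of Table 3 with a test of the PSQ total as a continuous outcome: ANCOVA or a linear model for the exit score with group, the baseline score and the covariates that Quantitative Analyses already plans. Use a rank-based alternative if the score is clearly non-normal. The Study Objectives section lists parenting stress among the baseline measures, so the baseline score should be available. State that this analysis decides hypothesis 5 and how the repeated measures ANOVA relates to it. Keep any PSQ cut-off categories descriptive and give their source.

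Optional: for Satisfaction-A and the three-point motivation items, use an ordinal test or model, or define a Satisfaction-A sum score in advance.

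The main change is one cell. With the optional part it touches four entries: PSQ, Satisfaction-A, youth motivation items and parent motivation items. No new data are needed. The Discussion says that data collection has ended and analysis has begun, so the change should be recorded before the PSQ group comparison is seen or, failing that, reported as a change of plan.
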